### 4.3. Description of the measures taken to reduce and avoid bias

#### Random sampling

Not applicable

#### Methods of blinding

Not applicable

### 4.4. Experimental drugs

#### 4.4.1 Description of the dose and methods of administration of the experimental drug(s)

Eplerenone 25 mg/day or 50 mg/day as a single dose by mouth to be taken every day of the study: 25 mg/day during steps 1 and 2, then 50 mg/day during step 3.

This treatment will be provided to the patients by the promoting centre. The pharmacy associated with this study is the pharmacy of the CHU, Reims (Hôpital Robert Debré), and the pharmacist responsible for this study is [name].

#### **4.4.2 Description of the unit form, packaging and labelling of the experimental drug(s).**

##### **Eplerenone**

Medicine commercially available in boxes of 28 tablets, available individually from the hospital pharmacy of the CHU, Reims

Eplerenone is available as a yellow film-coated tablet with the inscription « Pfizer » on one surface and « NSR » and « 25 » (or « 50 » depending on the dose) on the other.

##### **Cyclosporine**

Medicine commercially available in boxes of 50 to 60 soft capsules, available individually from the hospital pharmacy of the CHU, Reims. CsA is available as a soft capsule in doses of 10, 25, 50 or 100 mg.

#### **4.5. Anticipated duration of participation of subjects and description of the chronology and duration of all periods of the study (including follow-up)**

##### **4.5.1 Expected duration of participation of subjects**

The maximum participation of patients taking part in the study in group A will be 3 steps of 8 weeks, thus 24 weeks in total.

The maximum participation of patients taking part in the study in group B will be the 2 final steps of 8 weeks (2 and 3), thus 16 weeks in total.

##### **4.5.2 Description of the chronology and duration of all periods of the study, including follow-up**

See section 4.2.

#### **4.6. Rules for permanent or temporary withdrawal from the study**

See Figure 1 and section 4.2

Withdrawal from the study is permanent: a patient who has left the study cannot re-enter the study.

##### **4.6.1 For participation of a patient in the study**

The participation of a patient finishes either at the end of the study (end of step 3) or after the development of an adverse event requiring the premature termination of eplerenone in this patient.

##### **4.6.2 For all or part of the study**

The end of the study will either be at the end of step 3 or after the development of a large number of adverse events requiring the premature termination of eplerenone in the patients as defined in section 4.2.

#### **4.7 Procedures for accounting of the experimental drug(s)**

Counting of the packaging by the pharmacy at the end of each step.

#### **4.8 Arrangements for the maintenance of blinding and procedure for the lifting of blinding, if relevant**

Not applicable

#### **4.9 Identification of all data to be collected directly from the observation files, which will be considered as source data**

The following data will be collected from the observation files:

##### **Demographic data**

Date of birth

Sex

Weight

Height

##### **Clinical data**

Systolic and diastolic arterial pressure, lying down and standing

Previous history: diabetes, arterial hypertension, obesity, cardiac failure, respiratory failure, myocardial infarction, other

Electrocardiogram: problems with rhythm, problems with conduction, problems with repolarisation

Particularities of the clinical examination: presence of oedema of the lower limbs

Other treatments taken during the study

Appearance of adverse events (anti-androgenic effects in particular)

##### **Biological data**

Kalaemia

Creatininaemia, eGFR (according to the MDRD formula)

Natraemia, natriuresis, fractionated sodium excretion

Creatininuria

Kaluresis

Proteinuria, albuminuria

Serum profile, urine profile

##### **Functional data**

Vascular resistance of the transplant

#### **4.10 Independent Surveillance Committee**

In accordance with article L1123-7 of the Public Health Code, transposing European Directive 2001/20/CE to French law, an Independent Surveillance Committee (ISC) will be set up by the study promotor. The constitution and function of the ISC will conform to the Guidelines on Data Monitoring Committees of the European Medicines Agency (JO n°377 of 30th November 2006). This committee will guarantee the scientific integrity of the study.

The promotor will name 3 independent experts who will meet:

- before the start of the study, in order to approve its method of functioning, the study protocol, the methods for declaring any suspected adverse events and the methods for stopping treatment defined in the protocol
- during the study at least once in order to evaluate the tolerance and efficacy of the study drug as well as to control the general quality and progress of the study
- at the end of the study in order to approve the general quality of the running of the study

Each meeting will consist of a detailed review in which the ISC will give its recommendations: carry on without modification, carry on with modification(s), or even stop the study. These recommendations will be sent to the promotor and to the investigators.

If necessary, the ISC could have access to all of the study data. In this study, all of the files will be monitored by the ISC. It will also be informed of all new data that question the pertinence of the study.

## **5. SELECTION OF SUBJECTS AND EXCLUSION FROM THE STUDY POPULATION**

### **5.1. Inclusion criteria**

Patients able to participate in the study should fulfil the following criteria:

- age  $\geq 18$  years at inclusion
- possess full legal capacity
- give their written consent
- be affiliated to a Social Security Regime
- have had a function renal transplant for at least 2 years at inclusion
- be treated with cyclosporine
- presenter a renal function estimated with the MDRD formula (Levey et al., 1999) between 30 and 50mL/min/1.73m^2

### **5.2. Exclusion criteria**

Patients able to participate in the study should not fulfil any of the following conditions:

- kalaemia  $\geq 5$  mmol/L at inclusion
- one of more previous episodes of severe hyperkalaemia ( $\geq 6$  mmol/L), whatever the cause
- be receiving treatment with a potassium exchange resin such as KAYEXALATE®
- an episode of acute rejection during the year prior to inclusion
- be pregnant or not using effective contraception during the study
- uncontrolled arterial hypertension
- orthostatic hypotension
- systolic arterial pressure  $\leq 110$  mmHg
- cardiac failure in the 3 months prior to inclusion or cardiac failure (NYHA classes III or IV)
- severe liver failure (Child-Pugh class C)
- an allergy to one of the components of eplerenone – INSPRA®
- be receiving treatment with spironolactone – ALDACTONE® or eplerenone – INSPRA®
- have a contraindication for which treatment cannot be stopped during the study: diuretic for hyperkalaemia, potassium salt, CYP3A4 enzyme inhibitor (such as itraconazole, ketoconazole, ritonavir, nelfinavir, clarithromycin, telithromycin, nefazodone)
- be receiving treatment with trimethoprim or digoxin
- be receiving treatment with alpha 1 blockers
- be receiving treatment with warfarin
- a malabsorption syndrome, an anomaly of galactose metabolism, galactase deficiency
- be receiving treatment with a non-steroidal anti-inflammatory drug, a lithium-based treatment, or other nephrotoxic treatment
- be receiving treatment with double-blockade of the RAAS by the association ACE inhibitor and ARA2
- be a protected patient (under supervision, guardianship, under the protection of the law..)

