### **2.3. Summary of the benefits (if applicable) and the expected and known risks for subjects taking part in the study**

The expected benefits for patients participating in this study, taking into account its short duration, are small.

The expected benefits for society are essentially the possibility of carrying out a further study on the efficacy of eplerenone for the prevention of CsA nephrotoxicity. Currently, there are no drugs that can limit the renal toxicity of CsA. The aim of this future study will be to investigate the effect of eplerenone on the loss of renal function of renal transplant patients treated with CsA: the effect could be a longer life-expectancy of renal transplants and thus a lower cost (compared to a return to extra-renal dialysis or even a new transplant). These beneficial effects could be shared by patients participating in a prospective study comparing eplerenone with placebo.

The adverse events linked to the use of MR antagonists can be divided into ionic effects (hyperkalaemia and hyponatremia via their diuretic effect) and anti-androgenic effects (gynecomastia, problems with the menstrual cycle, impotence, etc...) (Bertocchio and Jaisser, 2010, Bertocchio *et al.*, 2011). The use of MR antagonists is usually not advised in patients with renal failure due to the increased risk of hyperkalaemia, particularly if another RAAS antagonist is added.

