## **2.6. Description of the study population**

In this tolerance study, we wish to determine the therapeutic window between the minimum effective dose and the maximum tolerated dose (limiting this to 50 mg/day maximum) in renal transplant patients receiving CsA with altered renal function (with an eGFR between 30 and 50 mL/min/1.73m^2).

The use of eplerenone is currently contraindicated in patients with renal failure defined by a creatinine clearance of <50 mL/min/1.73m^2 because there have been no specific studies in this population. However, a large multicentre study in cardiac failure (Zannad *et al.*, 2011) recently investigated the effect of eplerenone from stage II of the NYHA classification: nearly one-third of patients presented with chronic renal failure with an eGFR <60 mL/min/1.73m^2.

Similarly, the association of eplerenone with CsA is usually contraindicated because there has been no specific study in this population. By carrying out a study in patients receiving CsA with altered renal function, we will have the best conditions to reveal the major adverse event anticipated: hyperkalaemia.

We will select patients who have been transplanted for more than 2 years because this is when the doses of immunosuppressants and renal function are stable. Furthermore, from the end of the 2nd year of transplantation, the risk of acute rejection is low. We will exclude, for the same reasons, patients who have had an episode of acute rejection in the year prior to the date of inclusion. Furthermore, at 2 years after transplantation, nearly 50% of patients have histological signs of CsA toxicity (Nankivell *et al.*, 2003).

At an eGFR of <30 mL/min/1.73m^2, the lesions caused by CsA toxicity do not appear to be reversible. If the adverse effects of eplerenone are absent or acceptable, this molecule could be proposed to patients treated with CsA with a renal function >30 mL/min/1.73m^2.

Patients able to participate in the study should fulfil the following criteria (inclusion criteria):

- age ≥18 years on the date of inclusion
- possess full legal competence
- give their written consent
- be affiliated to a Social Security Regime
- have had a functional renal transplant for ≥2 years at the date of inclusion
- receiving treatment with CsA
- have a renal function estimated by the MDRD equation (Levey *et al.*, 1999) between 30 and 50 mL/min/1.73m^2

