Patients able to participate in the study should not fulfil any of the following criteria (exclusion criteria):

- kalaemia  $\geq 5$  mmol/L at inclusion
- one or more previous episodes of severe hyperkalaemia ( $\geq 6$  mmol/L), whatever the cause
- be receiving treatment with a potassium exchange resin such as KAYEXALATE®
- an episode of acute rejection during the 12 months prior to inclusion
- be pregnant or not using effective contraception during the study
- uncontrolled arterial hypertension
- orthostatic hypotension
- systolic arterial pressure  $\leq 110$  mmHg
- cardiac failure in the 3 months prior to inclusion or cardiac failure (NYHA stages III or IV)
- severe liver failure (Child-Pugh class C)
- allergy to one of the components of eplerenone – INSPRA®
- be receiving treatment with spironolactone – ALDACTONE® or eplerenone – INSPRA®
- have a contraindication for which treatment cannot be suspended during the study: diuretic for hyperkalaemia, potassium salts, CYP3A4 enzyme inhibitor (such as itraconazole, ketoconazole, ritonavir, nelfinavir, clarithromycin, telithromycin, nefazodone)
- be receiving treatment with trimethoprim or digoxin
- be receiving treatment with alpha 1 blockers
- be receiving treatment with warfarin
- a malabsorption syndrome, an anomaly of galactose metabolism, galactase deficiency
- be receiving treatment with a non-steroidal anti-inflammatory drug, a lithium-based treatment, or any other nephrotoxic treatment
- be receiving treatment with double-blockade of the RAAS by the association ACE inhibitor and ARA2
- be a protected patient (under supervision, guardianship, placed under the protection of the law..)

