**Table 1. Timetable for clinical and biological follow-up of group A**

|                                                           | Etape 1 |    |    |     |     |     |     |     |     |          | Etape 2 |    |     |     |     |     |     |     |          |    | Etape 3 |     |     |     |     |     |     |     |   |  |
|-----------------------------------------------------------|---------|----|----|-----|-----|-----|-----|-----|-----|----------|---------|----|-----|-----|-----|-----|-----|-----|----------|----|---------|-----|-----|-----|-----|-----|-----|-----|---|--|
|                                                           | J0      | J2 | J7 | J14 | J21 | J28 | J35 | J42 | J49 | J56 = J0 | J2      | J7 | J14 | J21 | J28 | J35 | J42 | J49 | J56 = J0 | J2 | J7      | J14 | J21 | J28 | J35 | J42 | J49 | J56 |   |  |
| Recueil du consentement                            | x       |    |    |     |     |     |     |     |     |          |         |    |     |     |     |     |     |     |          |    |         |     |     |     |     |     |     |     |   |  |
| Clinique                                           |         |    |    |     |     |     |     |     |     |          |         |    |     |     |     |     |     |     |          |    |         |     |     |     |     |     |     |     |   |  |
| Pression Artérielle                                       | x       |    |    | x   |     | x   |     |     |     | x        |         |    |     |     | x   |     |     |     | x        |    |         | x   |     | x   |     |     |     |     | x |  |
| Recherche d'effets indésirables                           | x       |    |    | x   |     | x   |     |     |     | x        |         |    |     |     | x   |     |     |     | x        |    |         | x   |     | x   |     |     |     |     | x |  |
| Poids                                                     | x       |    |    | x   |     | x   |     |     |     | x        |         |    |     |     | x   |     |     |     | x        |    |         | x   |     | x   |     |     |     |     | x |  |
| Electrocardiogramme                                       | x       |    |    |     |     | x   |     |     |     | x        |         |    |     |     | x   |     |     |     | x        |    |         |     |     | x   |     |     |     |     | x |  |

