#### **5.3.1 Criteria and modalities for the premature termination of treatment or exclusion of a subject from the study**

A patient participating in the study leaves the study when they:

- 1) present with at least one of the adverse event criteria requiring the cessation of eplerenone treatment:
  - hyperkalaemia  $\geq 6$  mmol/L and/or hyperkalaemia  $\geq 5.5$  mmol/L under 2 spoon-measures/day of KAYEXALATE®
  - acidosis revealed by an alkaline reserve of  $\leq 15$  mmol/L
  - systemic arterial hypotension revealed by a systolic arterial pressure  $< 100$  mmHg
  - orthostatic hypotension defined by a decrease in systolic arterial pressure of  $> 20$  mmHg in the 3 minutes following standing
  - acute renal failure defined by an increase in creatininaemia of  $> 30\%$  in comparison with its value at inclusion
  - all other unexpected adverse events requiring the termination of eplerenone treatment
- 2) present with an indication for treatment that is contraindicated in association with eplerenone (trimethopim, digoxin ...)

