### **6.2. Associated medicines and treatments allowed or forbidden by the protocol, including rescue medications**

In cases of the development an adverse event, other treatments could be necessary for the realisation of this study:

- sodium polystyrene sulfonate (Kayexalate®): this is a powder for suspension administered orally or rectally and sold in bottles of 454 g with a measuring spoon; it is administered daily to treated hyperkalaemia

- sodium bicarbonate®: this consists of an extemporaneous capsule preparation containing 500 mg of sodium bicarbonate; it is administered daily to treat metabolic acidosis.

These treatments will be given to the patients by the promotor. The pharmacy associated with this study is the pharmacy of the CHU, Reims (Hôpital Robert Debré); the pharmacist responsible for the study is [name].

During this study, no medicine or treatment (except for those listed in the exclusion criteria) is forbidden but they should be mentioned as quickly as possible to the investigators and noted in the observation folder.

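### The exclusion item on diuretics in sections 2.6 and 5.2 is worded in reverse, so potassium-sparing diuretics other than spironolactone are not literally excluded or forbidden

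*Protocol*

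**What the plan says.** The protocol gives its exclusion criteria twice. Section 5.2 excludes patients who "have a contraindication for which treatment cannot be stopped during the study: diuretic for hyperkalaemia, potassium salt, CYP3A4 enzyme inhibitor", followed by examples of CYP3A4 inhibitors. Section 2.6 has the same item with one verb changed: "have a contraindication for which treatment cannot be suspended during the study: diuretic for hyperkalaemia, potassium salts, CYP3A4 enzyme inhibitor".

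A separate line in each list excludes anyone who would "be receiving treatment with spironolactone" or with eplerenone already. No other potassium-sparing diuretic is named in either list, and no term for the class appears.

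Three other sections bear on the point:

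- Section 6.2 ties the rule on concomitant medicines to the exclusion list: "no medicine or treatment (except for those listed in the exclusion criteria) is forbidden". Other medicines need only be reported and recorded.
- Section 5.3.1, item 2, takes out of the study patients who "present with an indication for treatment that is contraindicated in association with eplerenone", with trimethoprim and digoxin as examples in an open list.
- Section 2.3 states that "The use of MR antagonists is usually not advised in patients with renal failure due to the increased risk of hyperkalaemia", and section 2.6 speaks of "the major adverse event anticipated: hyperkalaemia".

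**The concern.** A diuretic for hyperkalaemia is, in plain English, one prescribed to bring potassium down. In a list of treatments to be kept away from eplerenone, the drugs of concern are those that push potassium up. The phrase therefore points the wrong way in an eligibility rule, and section 6.2 makes that rule the only list of forbidden medicines during the study.

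The stake is mainly safety. The patients have an eGFR of 30 to 50 mL/min/1.73m² and take cyclosporine; section 2.6 says eplerenone is contraindicated on the first ground and usually contraindicated on the second. A second potassium-raising diuretic on top of eplerenone would be an avoidable hazard. It could also add a hyperkalaemia event to the primary criterion in section 4.1 for a reason other than eplerenone alone, because that criterion counts events without attributing cause.

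**Working it through.** The point concerns wording and the protocol gives no figure for it, so the check sets the relevant sections side by side.

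**Step 1: which sense does the context require?** Both lists introduce the item as a contraindicated treatment and place it next to potassium salts and CYP3A4 inhibitors. Potassium salts raise potassium, and a potassium-lowering diuretic has no reason to stand beside them. The same lists already exclude an entry potassium of 5 mmol/L or more, any past episode of 6 mmol/L or more, and current use of a potassium exchange resin. Patients being treated for high potassium are thus largely dealt with elsewhere. Sections 2.3 and 2.6 both name hyperkalaemia as the risk to guard against. The intended sense is a diuretic that causes hyperkalaemia.

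**Step 2: does another line of the list cover such diuretics?** Seven other lines in each list exclude patients by current drug treatment:

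| Line | Covers other potassium-sparing diuretics? |
|---|---|
| Potassium exchange resin | No |
| Spironolactone or eplerenone | These two drugs only |
| Trimethoprim or digoxin | No |
| Alpha 1 blockers | No |
| Warfarin | No |
| NSAID, lithium or other nephrotoxic drug | Not named |
| ACE inhibitor combined with ARA2 | No |

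An agent such as amiloride or triamterene (examples supplied here, not by the protocol) is not named in any line. The item under discussion is the only one that could exclude it, and its literal wording does not.

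**Step 3: does the rule on concomitant medicines cover them?** Section 6.2 forbids only what the exclusion list contains. With the item read literally, another potassium-sparing diuretic is permitted during the study.

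**Step 4: does the withdrawal rule cover them?** Section 5.3.1, item 2, is open-ended and could be applied when a need for a contraindicated drug arises during the study. It names no diuretic and does not govern who may enter, so it is a partial backstop and only on study.

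**Result.**

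| Stage | Item read literally | Item read as intended |
|---|---|---|
| Entry on another potassium-sparing diuretic | Not excluded | Excluded if the drug cannot be stopped |
| Use during the study (6.2) | Not forbidden | Forbidden |
| New indication during the study (5.3.1, item 2) | Possibly caught | Caught with a clear reference |

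**The case against.** The strongest reply is that this is a translation slip with little practical effect. The text reads as an English rendering of a French protocol for one French centre: the consent row of Tables 1 and 2 is still headed "Recueil du consentement", and the adverse event form is in French. Nothing shows that the investigators worked from the English wording. The item also largely corrects itself, because the literal sense is implausible beside potassium salts, and its readers are transplant nephrologists alert to hyperkalaemia.

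The protocol also limits the harm if such a diuretic were missed. Potassium must be below 5 mmol/L at entry and is then measured on D2 and weekly, with the result passed on the same day (section 4.2). Section 8.2 sets a graded response and asks patients to report new treatments, and section 6.2 asks for other medicines to be reported quickly.

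All of this stands, and it is why the point is minor. It does not remove the error. The phrase is the same in both lists, it is a rule on eligibility, and section 6.2 relies on it. Whether a medicine is allowed should not depend on the reader inverting a phrase.

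**Conclusion.** The wording is wrong in both places and should be corrected, as a minor safety correction. The conclusion rests on an inference from context, which is strong, that potassium-raising diuretics are meant. The protocol does not say how many eligible patients take another potassium-sparing diuretic, and the number may be zero.

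Three stronger readings are tempting, and the documents do not support them.

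- **That the protocol intends to allow these diuretics with eplerenone.** The heading of the item and the drugs beside it point the other way.
- **That the wording distorts the stopping rules or error rates.** The protocol gives neither the frequency of such use nor the event risk under it, so any figure would rest on assumption alone. The sample size and the stated error rates do not depend on this phrase.
- **That a wash-out before D0 is missing, because the item lets a patient enter by stopping a listed drug.** Tables 1 and 2 are follow-up timetables that start at D0. Patients come from the centre's own cohort, already followed there for at least two years (section 9.3), so a drug can be stopped beforehand in ordinary care. Section 12.3 on information and consent, which could cover steps before inclusion, was not available for this check. The number of patients concerned and the direction of any carry-over on creatinine are both unknown.

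**What to change.** In sections 2.6 and 5.2, replace the phrase with *diuretics that raise potassium (potassium-sparing)* and leave the rest of the item as it is. Section 6.2 then forbids these drugs during the study through its existing reference to the exclusion list, and needs no change of its own. If a French original is the working document, check its wording first; should it already be right, only the English text needs correcting.

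The cost is one phrase in two places. Sample size, visits, stopping limits and analysis are unchanged.
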